This is a multi-center, randomized, placebo-controlled, double-blind, cross-over study. A cross-over design is adopted to avoid disadvantage in subjects who are allocated in the placebo treatment because amantadine has beneficial effects against PD.

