## 6. Interventions

Patients who meet the criteria and seen between March 2007 and February 2008\*1 were considered for the study.

The Arm 1 intervention consisted of an observation period (2-3 weeks), an administration of amantadine hydrochloride period (27 days), a washout period (15 days), and an administration of placebo period (27 days). The Arm 2 intervention consisted of an observation period, placebo period, a washout period, and an administration of amantadine period. Amantadine was escalated step-by-step (100 mg for 7 days, 200 mg for 7 days and 300 mg for 7 days). Placebo is also administered in a

similar manner. The detailed schedule is shown in the Table 1.

Table 1. Schedule of the study

|          | Visit      | UPDRS
/Rush
dyskinesia
scale | blood sampling | video
recording | Arm 1                      | Arm 2                      |
|----------|------------|---------------------------------------|----------------|--------------------|----------------------------|----------------------------|
| Visit 1  | Day -13    | ○                                     | ○              |                    | Observation period (2-3 W) | Observation period (2-3 W) |
|          | Day -12    |                                       |                |                    |                            |                            |
|          | Day -11    |                                       |                |                    |                            |                            |
|          | Day -10    |                                       |                |                    |                            |                            |
|          | Day -9     |                                       |                |                    |                            |                            |
|          | Day -8     |                                       |                |                    |                            |                            |
|          | Day -7     |                                       |                |                    |                            |                            |
|          | Day -6     |                                       |                |                    |                            |                            |

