| Visit 10 | Day 70 ±3日 | ○                                     |                |                    |                            |                            |
|          | Day 71     |                                       |                |                    |                            |                            |
|          | Day 72     |                                       |                |                    |                            |                            |
|          | Day 73     |                                       |                |                    |                            |                            |
|          | Day 74     |                                       |                |                    |                            |                            |
|          | Day 75     |                                       |                |                    |                            |                            |

● plasma concentration of amantadine  
○ CBC, Chemical analysis  
(○) on site investigation or telephone contact

Escalation of trial drugs could be discarded if the patients desired no escalation or adverse effects were detected.

Allocation to Arm 1 or Arm 2 is determined according to a computer-generated randomization plan that includes stratification by severity of dyskinesia (ADL-interfering or not-interfering).

At the end of the observation period and at the day 21 of the amantadine or placebo treatment periods, UPDRS-3, UPDRS-4, video recording of dyskinesias and Rush Dyskinesia Rating Scale\*2 (RDRS), medication, blood sampling, and type of dyskinesias (peak dose, end-of-dose, or biphasic dyskinesia) will be checked. Plasma concentrations of amantadine hydrochloride will be determined at the day 21 of amantadine or placebo periods and at the end of washout period.

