#### 7. Target sample size

Target sample size is 60 interventions. The sample size was determined based on the previous study by Snow et al., in which dyskinesia score is expected to be improved by 1.1 (1.6) (mean (SD) points on the UPDRS-IVa by amantadine. It was estimated by power analysis comparing the two means, and calculated as 30 (60 interventions) to achieve a power greater than 80% and an error of 0.05 in the crossover test.

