## 12. Analysis

### Primary outcome measure:

Primary outcome measure is the difference of Rush Dyskinesia Scale from baseline after amantadine hydrochloride and after placebo administration.

The changes of scores from baseline will be compared between amantadine and placebo interventions.

Changes of RDRS will be categorized into improved and not-improved, and data will be analyzed using repeated measure logistic regression incorporating treatment effects (placebo vs active) and period effects (interaction of order effect and carry-over effect).

*P* values of less than 0.05 are considered statistically significant.

Rush Dyskinesia Scale is scored based on video recording of dyskinesias.

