### Secondary outcomes:

Secondary outcome measures include the difference of UPRDS-III, IVa, and IVb from baseline after amantadine hydrochloride and after placebo administration. The changes of score from baseline will be compared between amantadine and placebo interventions.

UPDRS-III is scored on neurological examination performed by neurologists

UPDRS-IV is scored by interview.

Changes of UPDRS-IVa will be analyzed using a mixed linear model incorporating treatment effects (placebo vs active) and period effects (interaction of order effect and carry-over effect).

In addition secondary outcome measures include the correlation between blood concentrations of amantadine hydrochloride and the UPDRS (parts III and IV) and Rush Dyskinesia Scale changes.

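### Both efficacy models define the period effect as an order-by-carry-over interaction, which a two-period crossover cannot define, so the treatment estimate depends on coding the protocol leaves open

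*Protocol*

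**What the plan says.** The design is stated plainly: "This is a multi-center, randomized, placebo-controlled, double-blind, cross-over study". Section 6 gives two arms that take amantadine and placebo in opposite order, separated by "a washout period (15 days"), so there are two sequences and two periods.

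Section 12 analyses improvement on the Rush scale by repeated-measures logistic regression "incorporating treatment effects (placebo vs active) and period effects (interaction of order effect and carry-over effect"). The change in UPDRS-IVa is analysed "using a mixed linear model incorporating treatment effects (placebo vs active) and period effects (interaction of order effect and carry-over effect"). The parenthesis is the same in both. Neither place defines the order or carry-over term or gives its coding, and neither describes period as first versus second.

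The sample size in section 7 rests on a within-patient design: "calculated as 30 (60 interventions) to achieve a power greater than 80% and an error of 0.05 in the crossover test".

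Section 6 also has plasma amantadine measured "at the day 21 of amantadine or placebo periods and at the end of washout period". Table 1 marks the clinical scales and a plasma sample at Visit 6 (Day 42). By the stated durations, 27 + 15 = 42 days, this visit falls at the end of washout.

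**The concern.** The parenthesis does not describe a period effect. A period effect is a systematic difference between the first and second treatment periods, whichever treatment is given. Order (sequence) and carry-over are different ideas. In this design they share one degree of freedom, so an interaction between them has no contrast of its own to estimate.

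An analyst has to turn the phrase into a column of a design matrix, and several columns are defensible. Some keep the comparison of each patient with himself or herself. Others make the treatment coefficient a parallel-group comparison in period 1. That choice can decide the significance of the primary result. The protocol's section on handling of study data places analysis after the treatment code is opened, so under this text alone the choice could be made with allocation known.

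**Working it through.** **Inputs.** Mean improvement 1.1, SD 1.6, 30 patients, error 0.05 (section 7). Assumed, because the protocol does not give them: two-sided testing, a 15/15 split by sequence, and within-patient correlation rho between periods (0 to 0.8 shown). The protocol does not say whether 1.6 is the SD of a within-patient difference or of one score, so both are carried.

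**The plan's own figure.** For 80% power:
- a paired comparison needs (1.6 x (1.96 + 0.84)/1.1)^2, which rounds up to 17 patients (19 with the t distribution);
- two independent means need 34 per treatment (35 with t), or 27 one-sided.

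None of these returns 30. The paired reading at 30 patients does satisfy the claim of more than 80%: SE = 1.6/sqrt(30) = 0.292, and power = Phi(1.1/0.292 - 1.96) = 96.5% (95.3% with t). How 30 was obtained is a separate matter and does not affect what follows.

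**Which contrast estimates treatment.** Write the four cell means as A1P1 (amantadine), A1P2 (placebo), A2P1 (placebo) and A2P2 (amantadine), where A is arm and P is period. Let m be the intercept, t treatment, p period, s sequence and c first-order carry-over.

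- With a sequence term: A1P1 = m + t, A1P2 = m + p, A2P1 = m + s, A2P2 = m + s + p + t. Then t = 0.5(A1P1 - A1P2 - A2P1 + A2P2), the within-patient contrast.
- With a first-order carry-over term: A1P1 = m + t, A1P2 = m + p + c, A2P1 = m, A2P2 = m + p + t. Then t = A1P1 - A2P1, which is period 1 only.
- With a treatment-by-period term: sum coding gives the within-patient contrast; coding with period 1 as reference gives period 1 only.
- With sequence and carry-over together: five columns, rank 4, so the two are aliased.
- With the literal product of sequence and carry-over: all zeros if Arm 2 is coded 1, or the carry-over column itself if Arm 1 is coded 1.

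The full-rank models with one extra term (sequence, carry-over or treatment-by-period) all saturate the four means. Their fitted means are identical, so goodness of fit cannot choose between them.

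**Variance.** With score variance v, the crossover contrast has variance 2v(1 - rho)/30 and the period-1 contrast 2v/15. The ratio is 2/(1 - rho): 2 at rho 0, 4 at 0.5, 10 at 0.8.

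**Power for UPDRS-IVa (normal approximation).** If 1.6 is the SD of the difference, one score has SD 1.6/sqrt(2(1 - rho)). At rho 0.5 that is 1.6, so the period-1 SE = 1.6 x sqrt(2/15) = 0.584 and power = Phi(1.1/0.584 - 1.96) = 47%.

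| rho (assumed) | 1.6 = SD of difference: crossover | period 1 only | 1.6 = SD of one score: crossover | period 1 only |
|---|---|---|---|---|
| 0 | 96% | 76% | 76% | 47% |
| 0.25 | 96% | 64% | 87% | 47% |
| 0.5 | 96% | 47% | 96% | 47% |
| 0.8 | 96% | 22% | about 100% | 47% |

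**Binary primary outcome, illustration only.** The protocol gives no response rates. A simulated GEE logistic analysis (30 patients, latent correlation 0.5, 400 trials) with assumed improvement of 60% v 25% gave power of about 94% with treatment and period, and 46% with a first-order carry-over term added.

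**The case against.** The best defence is that the sentence lists only treatment and period effects, and that the parenthesis is a clumsy gloss on what the period term absorbs. Read that way, the fitted model is treatment plus period with repeated measures, close to the fix below. Detailed coding may also sit in an analysis plan that is not shown. The first reading is possible but is not what the words say. The second would excuse silence, but here the protocol defines the term, and defines it wrongly, in both models.

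Four stronger inferences are tempting, and the document does not support them.

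- A reader might infer that any model mentioning carry-over uses period 1 only. It does not: a sequence main effect or a sum-coded interaction keeps the within-patient contrast. The loss belongs to particular codings.
- A reader might infer that the model cannot be fitted. The rank deficiency arises only if order and carry-over enter as separate terms, which no section lists. If software drops the carry-over column as redundant after sequence, treatment is still the within-patient contrast.
- A reader might infer that carry-over cannot be estimated at all. It cannot be separated from sequence using the two end-of-period values. It is estimable between patients if no sequence effect is assumed, and the Visit 6 ratings and end-of-washout plasma levels also bear on it.
- A reader might infer that power is halved. That matches rho of about 0.5 only. The protocol gives no correlation, its power inputs concern a secondary outcome, and the binary illustration rests on assumed response rates.

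**Conclusion.** The definition is wrong in both efficacy models, including the primary one, and should be corrected. Period is first versus second period, and order and carry-over are aliased in this design, so the stated interaction is not a definable term.

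The harm is conditional. If the phrase is coded as a first-order carry-over term, or as a treatment-by-period term with period 1 as reference, the treatment test rests on about 15 v 15 patients with its variance inflated by 2/(1 - rho). For rho from 0 to 0.8, UPDRS-IVa power is then 76% down to 22% on one reading of the SD, and 47% on the other. Every one of these falls below the planned 80%. These figures rest on equal allocation, two-sided testing and an assumed rho. They do not measure the power of the primary Rush analysis, for which the protocol gives no inputs. If the phrase is coded as a sequence term, the within-patient contrast is kept.

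**What to change.** In section 12, under both the primary and the secondary outcomes, replace the parenthesis. State fixed effects for treatment (amantadine or placebo) and period (first or second), with sequence (Arm 1 or Arm 2) optional, and patient as the repeated unit in the logistic model and the random effect in the linear one. State that the model used for the treatment test contains no carry-over term.

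Assess washout adequacy descriptively from data already planned: end-of-washout plasma amantadine, and Visit 6 ratings set against Visit 2 by sequence.

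The cost is two sentences and no new data. The small downside is that the treatment estimate then assumes the washout is adequate. The crossover design already relies on that, and the planned measurements allow it to be examined.

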### Secondary outcomes:

Secondary outcome measures include the difference of UPRDS-III, IVa, and IVb from baseline after amantadine hydrochloride and after placebo administration. The changes of score from baseline will be compared between amantadine and placebo interventions.

UPDRS-III is scored on neurological examination performed by neurologists

UPDRS-IV is scored by interview.

Changes of UPDRS-IVa will be analyzed using a mixed linear model incorporating treatment effects (placebo vs active) and period effects (interaction of order effect and carry-over effect).

In addition secondary outcome measures include the correlation between blood concentrations of amantadine hydrochloride and the UPDRS (parts III and IV) and Rush Dyskinesia Scale changes.

#### Safety analysis

The prevalence of adverse events will be compared between amantadine and placebo interventions.

#### [Response to adverse events]

In case of adverse events escalation of the IP should be discarded, the IP should be de-escalated or ceased if necessary. Adverse events should be reported to the principal investigator and the study supervisor.

#### [Handling of study data]

Data will be collected and fixed by the principal investigator. Data will be analyzed after key-open.

#### [Registration of the study]

The study will be registered in UMIN-Clinical Trials Registry (UMIN-CTR).

#### [Publication of the study]

The study will be published to the journal under the names of the investigators, or the name of study group if necessary.

ADDENDUM 1.

---Video recording instruction---

Please record dyskinesia (involuntary movement) as follows:

1. Record the patient walking (for 10 meters).
2. Record the patient drinking from a cup.
3. Record the patient putting on a coat and button clothing.

Please record the movement of the head, trunk and upper and lower extremities of patients.

## ADDENDUM 2

This protocol has been approved by the ethical review board of National Utano Hospital, National Hospital Organization (18-15) on March 1, 2007, and then approved by the institutional ethics review board at each participating site.\*

\* the Bioethics Committee of Utano National Hospital, the Ethics Committee of National Center for Neurological and Psychiatric Disorders , Ehime University Hospital IRB, the Ethics Committee of Miyagi National Hospital, the Ethics Committee of Mie University Hospital, the Ethics Committee at Sagamihara National Hospital, the Ethical Committee of Research Institute for Brain and Blood Vessels Akita, the Ethical Review Committee of National Defense Medical College, the Ethics Committee of Nishitaga National Hospital, Bioethics Committee of Jichi Medical University, and the Ethics Committee of Saigata National Hospital, and the Institutional Review Board of Kagawa Prefectural Central Hospital
